## Abstract

**Background:**

Cardiovascular disorders (CVD) are the single greatest cause of mortality worldwide. In the UK, the National Health Service (NHS) has launched an initiative of health checks over and above current care to tackle CVD. However, the uptake of Health Checks is poor in disadvantaged communities. This protocol paper sets out a UK-based study (Sussex and Nottingham) aiming to co-produce a community delivered CVD risk assessment and coaching intervention to support community members to reduce their risk of CVD.

The overall aim of the project is to implement a tailored-to-context community engagement (CE) intervention on awareness of CVD risks in vulnerable populations in high, middle and low-income countries. The specific objectives of the study are to enhance stakeholder’ engagement; to implement lifestyle interventions for cardiovascular primary prevention, in disadvantaged populations and motivate uptake of NHS health checks.

**Methods:**

This study uses both qualitative and quantitative methods in three phases of evaluation, including pre-, per- and post-implementation. To ensure contextual appropriateness the ‘Scaling-up Packages of Interventions for Cardiovascular disease prevention in selected sites in Europe and Sub-Saharan Africa: An implementation research’ (SPICES) project will organize a multi-component community-engagement intervention. For the qualitative component, the pre-implementation phase will involve a contextual assessment and stakeholder mapping, exploring potentials for CVD risk profiling strategies and led by trained Community Health Volunteers (CHV) to identify accessibility and acceptability. The per-implementation phase will involve healthy lifestyle counselling provided by CHVs and evaluation of the outcome to identify fidelity and scalability. The post-implementation phase will involve developing sustainable community-based strategies for CVD risk reduction. All three components will include a process evaluation. A stepped wedge cluster randomised trial of the roll out will focus on implementation outcomes including uptake and engagement and changes in risk profiles. The quantitative component includes pre and post-intervention surveys. The theory of the socio-ecological framework will be applied to analyse the community engagement approach.

**Discussion:**

Based on the results ultimately a sustainable community engagement-based strategy for the primary prevention of CVD risk will be developed to enhance the performance of NHS health care in the UK. The Trial Registration number is ISRCTN68334579.

## Introduction

Cardiovascular disorders (CVD) are the single greatest cause of mortality worldwide each year, estimated to contribute to 31% of all deaths globally [1]. Tackling CVD is an international priority and there have been many global initiatives such as the “Global Hearts” programme, a package launched by the World Health Organisation (WHO) and partners, to enhance the prevention and control of CVD. Some risk factors for CVD are non-modifiable, such as age, ethnicity and family history [2]. Some other risk factors for CVD are modifiable, such as smoking, a lack of physical activity, being overweight, lower consumption of fruit and vegetables, high blood pressure, diabetes and high cholesterol [2]. These risk factors can be changed through lifestyle or behavioural modifications. There is evidence of a social gradient in the prevalence of CVD, which points to associations between social and financial deprivation, vulnerability and risk factors for CVD [3]. In 2015, CVD was the leading cause of mortality in the context of all chronic diseases, accounting for 27 and 25% of deaths in men and women respectively, in the UK [2]. Coronary heart disease (CHD) and stroke were the main CVDs responsible for this mortality of men and women across all ages. As per British Heart Foundation report in 2017 CVD has a huge financial burden with annual associated healthcare costs estimated to be £9 billion annually in the UK [2]. The UK has a standardised CVD death rate of 265.1 per 100,000 [2].

In the UK, the National Health Service (NHS) has launched the Health Check initiative aimed to reduce CVD. It is a national risk assessment and management programme, free to adults aged 40 to 74 living in England, who do not currently have any vascular disorders and are not being treated for certain risk factors such as diabetes [4]. It aims to assess the 10-year risk of CV events and disorders. Risk is assessed using QRISK2 [5], a tool which involves collection of the following information: age, gender, ethnicity, smoking status, family history of CHD, body mass index (BMI), cholesterol test, systolic and diastolic blood pressure, levels of physical activity, and alcohol consumption. Attendees receive a low (< 10% chance of event in 10 years), medium (> 10% but < 20%), or high (> 20%) 10-year cardiovascular (QRISK2) score. Above the 10% cut-off, attendees are offered a discussion with a qualified person, such as a nurse, about lifestyle and motivation to change, which may include goal setting and plans for follow up. Patients may also be offered medication for cholesterol and blood pressure. The NHS Health Check is recommended to be undertaken every 5 years.

Modelling predicted that the NHS Health Check could prevent 1600 heart attacks and strokes each year if implemented as intended [6]. Whilst evidence suggests that the Health Check programme has the potential to reduce CVD events and has therefore been rolled out nationally across the UK, its implementation has been poor, especially in some of the most disadvantaged groups at highest risk of developing CVD. In 2014, Public Health England (PHE) issued a call for action to increase the uptake rate of NHS Health Checks to 75% [7] and to increase awareness of risk and engagement with existing resources. Yet, as of 2017, current uptake remains far from this target with current predictions suggesting only 40% of the eligible population will receive one [8], due to the fact that uptake is low (48%) even when Health Checks are offered [8, 9].

Data from some regions with very large ethnic minority communities and socio-economically challenged populations showed that only 45% of patients who were invited for the check attended and subsequently received some form of counselling when they needed it. The current study uses the term socio economically challenged (SEC) or disadvantaged population based on a study where SEC was assessed using the Townsend score using 2001 census-derived measures of overcrowding, car ownership and education available at lower super output area. This has been found by linking the individuals’ postcode to lower super output area, approximately 150 households [10]. Authors have also suggested that higher uptake in SEC communities would reduce the possibility of exacerbation of inequalities [10]. Difficulty with accessing general practices, especially among socially vulnerable groups, has been highlighted as a common barrier to attendance at Health Checks [11]. A community-based engagement approach, which takes the CVD risking profiling and affiliated advice processes outside of the formal healthcare facility setting, has the potential to improve access to Health Checks and could be an effective and scalable way for improving the implementation and uptake of Health Checks. Community engagement (CE) has been conceptualised as “the process of working collaboratively with and through groups of people affiliated by geographic proximity, special interest, or similar situations, to address issues affecting the well-being of those people” [12]. A review of community engagement interventions found them to be effective in improving health behaviours (such as physical activity), health consequences and psychological outcomes (i.e. self-efficacy and perceived social support) [13]. Community-based intervention programmes have been implemented to increase the uptake of cancer screening programmes. The programmes have been found to be effective in increasing outcomes such as recognition, receipt and maintenance of screening behaviours [14]. The CE approach offers the opportunity for task-shifting and owning the programme, whereby trained non-healthcare-professionals can perform CVD risk profiling assessments to individuals who might not otherwise be captured by the formal care pathway.

There is evidence that CVD risk assessments can be successfully delivered by Community Health Workers (CHWs), outside or inside the healthcare system. An observational study conducted in Bangladesh, Guatemala, Mexico and South Africa has demonstrated that CHWs who are inhabitants of their local communities and were fluent in the community’s predominant language, can perform community-based screenings to predict CVD risk as effectively as physicians and nurses when using the non-laboratory-based Gaziano CVD risk scoring tool [15]. CHWs were trained for 1–2 weeks, and results showed a 96.8% agreement between risk scores assigned by CHWs and healthcare professionals. However, a question remains whether the model taken in the global South could be transferrable to the global North, but it is at least plausible that a community-based engagement approach will be effective for increasing the uptake of CVD risk assessment, particularly in disadvantaged communities of the global North. There are examples in the global North on community engagement in health [16], and indeed the voluntary or ‘third sector’ have been considered key partners in the delivery of health promotion initiatives in the community [17].

Authors have argued that because of the current economic constraints with the formal healthcare system in the UK, the focus should be upon supplementing a service delivery model with an alternative community development model [18]. The key aspect is supplementing formal service delivery by utilizing communities’ ‘social capital’. The term ‘social capital’ describes the various resources that people may have through their relationships in families, communities and other social networks. Social capital bonds people together and helps them make links beyond their immediate friends and neighbours [19].

For this compassionate community approach to work, contextual appropriateness and cultural sensitivity of an intervention is crucial [20]. Following this argument, the SPICES project (Scaling-up Packages of Interventions for Cardiovascular disease prevention in selected sites in Europe and Sub-Saharan Africa) in two areas of England, East Sussex and Nottingham, will co-produce a multi-component community-engagement intervention focussed on delivering a Health Check-style CVD risk screening intervention. The UK SPICES project will use appropriate health coaching and follow-up, in a community setting [21] delivered by community volunteers. The specific objectives of the project are:
To explore with stakeholders the potential for a community engagement-based CVD primary prevention programme to support or enhance the NHS Health Check Programme.To co-produce with the communities an evidence-informed community-engagement intervention on CVD risk, based on the NHS Health Check model, tailored to the context in disadvantaged communities in East Sussex and Nottingham.To implement the intervention in the local communities where it was co-produced, and:assess its effectiveness versus routine care.assess the fidelity, feasibility, acceptability, uptake and scalability of the implementation.carry out a process evaluation of the intervention and its implementation.The SPICES Project is a Horizon 2020 project financed by the European Commission that aims to address the CVD burden [22]. The overall objective is to implement and evaluate a comprehensive cardiovascular disease (CVD) prevention and care program at the community level in five countries (Belgium, France, South Africa, Uganda, and UK), to identify and compare barriers and facilitators for implementation across study contexts and to develop a learning community. The intervention will be trialled and evaluated using a mixed methods approach using both qualitative and quantitative methods.

## Methods

### Theoretical model

SPICES is underpinned by the Consolidated Framework for Advancing Implementation Research (CFAIR; 23), and Reach, Effectiveness, Adoption, Implementation, and Maintenance (sustainability) framework /RE-AIM models [23]. It is a global health project, and thus needs a socio-ecological framework for consistency between teams [24]. This framework allows an understanding of the multifaceted and interactive effects of personal, social and environmental factors that determine behaviour; and for identifying behavioural and organisational leverage points and intermediaries for health promotion within organisations and communities.

### Study design

A mixed-methods research methodology will be applied, strategically combining qualitative and quantitative methods at both sites. This approach will allow us to model the iterative nature of coproduction and implementation research without compromising the rigour of the study [25, 26]. The study will take place in three phases:
Pre-intervention; when stakeholder mapping and local adaptation will be carried out.Per-intervention roll out, recruitment and evaluation.Post-intervention evaluations and feedback [27] Process evaluation will be conducted in all three phases.

### Processes

#### Stage 1: to explore the implementation context and co-produce the intervention

To explore the context where the implementation will take place we will carry out several mappings. These will give us the context for recruitment and implementation co-design.

They are as follows:
Mapping the potential stakeholders: Mapping of the stakeholders will be done to find out who are the key stakeholders, where they come from, and what they are looking for in relationship to the study objectives [28]. To engage the community, it is essential to map the community stakeholders (civil society organisations) as they are the gatekeepers of the community. Three levels of stakeholder mapping will be carried out, namely at macro, meso and micro levels.
*Macro-level*: Stakeholders will be identified via the existing link of PI of the project in the community through meetings with local public health or other relevant departments and CSOs and using online information. Interviews with this category of stakeholders will provide insights into implementation sustainability.*Meso-level*: A strategic community volunteer organisation mapping will be carried out to find out the relevant organisations, through which individual volunteers will be selected. This will be done in three ways; using online searches, personal contacts and snowballing. In-depth interviews will be conducted to co-design a sustainable intervention implementation.*Micro-level*: An exploration will be undertaken with volunteers and end-user groups to co-design an acceptable and feasible intervention implementation.Mapping the context: social mapping will be carried out to explore the lifestyle context of the community via observations.Training of volunteers by professional health trainers and researchers following the current NICE Public health guideline [PH6] ‘Behaviour change: general approaches’ [29].CVD risk profiling by trained community health volunteers (CHV) during the pre-implementation stage.

CHVs will be the persons who have been involved in health-related volunteering for example volunteers who worked in cancer prevention, health check, healthy lifestyle etc. programme. They will be involved in the screening of the CVD risk population and implement the designed intervention.

#### Expected intervention

The final elements of the intervention will be co-produced within each community setting, following the mapping exercises outlined above on the contextual barriers and enablers of intervention implementation. Data from each site will contribute to a holistic intervention. These four sites are geographically close to each other and have similarities in socio-economic status so it is likely that the interventions will be similar. However, although the core components are similar, implementation within a setting/organization could be different. As outlined in the CFAIR [30], interventions are usually composed of a core component which is essential and indispensable, and an adaptable periphery, which can and should be tailored to the specific setting and users.

##### Core components

Following identification of moderate to high risk for CVD, the intervention will consist of non-clinical (non-NHS) individual or group support sessions within the community, focus on motivating behaviour change. Each participant will be supported by trained SPICES researchers or community health workers to identify behaviour change goals, produce action plans to achieve them, and problem solve in cases of unexpected outcomes. All SPICES Interventions are theoretically grounded in the theory of behaviour change and deploy the strongest evidenced Behaviour Change Techniques (BCTs) from the literature: Goal Setting, Action Planning, Problem Solving, Motivational Interviewing, Feedback on progress towards goals, Feedback on the health impact. The use of these six BCTs are focussed in SPICES on five Target Behaviours: Reduce/cease smoking, Increase moderate physical activity, Reduce the fat, salt, and sugar content of the diet, Increase fibre, oily fish, fruit and vegetable content of the diet, Reduce sedentary hours.

##### Community adaptation

The exact elements of the support sessions will be tailored to individuals and their community context, will be determined during iterative co-design with community representatives, and will be drawn from the following [31, 32]:
Step-I - Goal setting

Every participant should receive specific healthy lifestyle counselling/feedback based on their individual item InterHEART assessment scores (the moderate group). The feedback will be based on a review of international guidelines conducted as formative work for the SPICES project intervention [33]. SPICES behaviour change support sessions will be based on the best-evidenced approaches to healthy lifestyle modification and community context and preferences.

The following screening self-report questionnaires assess the benefit of possible behaviour changes in relation to physical activities and dietary practices. Selected modified questionnaires will be used for measuring the impact of implementations;
International Physical Activity Questionnaire (http://www.sdp.univ.fvg.it/sites/default/files/IPAQ_English_self-admin_long.pdf) is an internationally validated instrument to capture information about weekly physical activity habits, behaviours and routines.The Dietary Approaches to Stop Hypertension Questionnaire DASH-Q is a self-reporting lifestyle questionnaire (https://www.bmj.com/content/357/bmj.j1794.full.print) to capture information about weekly dietary habits, routines and behaviours, based around ‘Dietary Approach to Stopping Hypertension’ [34].Current behaviours audit: Using food and physical activity diaries prepared by and provided to participants by the SPICES research team, participants will be encouraged to complete an audit of 1 week of current dietary and physical activity behaviours, habits and routines to establish a baseline from which goals for change and improvement can be set in negotiation with SPICES CHVs.The Attitudes and Beliefs about Cardiovascular Disease (ABCD) Risk Questionnaire, licenced under Creative Commons Attribution 4.0 International Licence, developed by Maria Woringer et al. [35]. to assess participant perception of personal heart health risk.The EQ-5D-5 L internationally validated Quality of Life self-reporting questionnaire.Step-II - Action planning by the participants

Participants will be asked to create an action plan with appropriate goal setting for two behaviours (diet and exercise habits) in relation to when, where and how they will undertake, for example, physical activity (based on the item stems used by Luszczynska & Schwarzer [36]; when the physical activity will be performed, where it will be performed, how often it will be performed. The way goals are reached and plans recorded will be co-designed with key stakeholders.
Step III - Problem-solving

CHVs will help participants to analyse any factors which may influence their ability to achieve the goals and to generate strategies which could help them overcome these barriers.

CHVs will use Motivational Interviewing techniques about health, social and environmental, and emotional barriers and consequences. Culturally and context-sensitive information will be provided (both verbally and in the form of leaflets) about the importance of eating healthily, being physically active, and not smoking for positive outcomes on physical and mental health.

#### Stage 2: intervention roll out, recruitment and evaluation

This will be an open-label, stepped wedge cluster randomised controlled trial, examining fidelity, feasibility, acceptability, uptake and scalability of the intervention.

#### Eligible population and setting

Economically disadvantaged, lower socio-economic status (SES) postcodes, will be identified using the overall Index of Multiple Deprivation [37]; Participants’ SES will be determined by their postcode of residence. Any resident aged 18 or above living in the study postcode areas will be eligible to take part in the baseline assessment for the study.
Study sample size and power calculation

The sample size calculation for the quantitative study used statistical modelling for a stepped wedge design, randomising community centres over time with the InterHEART score as the outcome (90% power for 5% significance, small effect size (Cohen’s D) = 0.25, intracluster correlation coefficient of 0.05, control clusters crossing to intervention in 4 steps, participant autocorrelation = 0.7 and cluster autocorrelation = 0.9), which requires a total of at least 144 persons. This needs approximately 200–300 people across the two sites as we expect a high level of attrition (as much as 50%). At least 1500 community members will need to be screened to achieve this recruitment [38].
(b)Recruitment of community health volunteers and trial participants

Community Health Volunteers (CHVs) will be recruited to perform CVD risk profiling assessments through a combination of ‘doorstep outreach’ and ‘intermediary organisation recruitment’ approaches in East Sussex and through existing community and neighbourhood groups with the assistance of partners such as Self-Help UK, the Renewal Trust, Nottingham CVS and others in Nottingham. For recruitment of trial participants, we will use similar community networks, and endeavour to use quota sampling, in that we will seek to ensure the inclusion of high, low and median income neighbourhood residents, citizens from the South Asian and African diasporas; and will encourage participants to refer others to the researchers who may be able to potentially contribute or participate in the study.
(c)Baseline screening of CVD risk

Participants will fill in the validated non-laboratory based InterHEART score to determine suitability for the trial. The InterHEART scoring tool requires minimal resources which is practical for use within the community. There is also evidence to suggest that the InterHEART can reliably predict the incidence of CVD and death in low, middle, and high-income countries for a mean follow-up of 4.1 years [39]. Risk is expressed as a score from the InterHEART: 0–9 (Low risk), 10–15 (moderate risk), and 16–48 (high risk). The InterHEART scoring tool will be inserted onto a mHealth platform so that the trained CHVs can easily administer them during community engagement and contact, and online data will directly reach the University repository in real time from the respondents’ device. The moderate risk (amber) score population will be selected for participation in the intervention (= score of 10 or higher), and will fill out the self-completion survey InterHEART scoring every 3 months [40].
(d)Clinical outcome and follow-up

The primary outcome will be the change in the CVD risk score among people who complete the community delivered CVD risk assessment and coaching (before/after and between groups). In addition, a by-product outcome will be gathered from participants identified as ‘high risk’ (who are not part of the sample) during the screening process. This group of participants will be signposted to their GP surgery requesting a) a formal CVD risk check-up and b) completed NHS Health Checks. The following secondary outcomes will be gathered from such participants identified as ‘high risk’: 1) Numbers of participants who a) self-referred (defined as having contacted their GP surgery requesting for a formal check-up) and b) completed the NHS Health Check, 2) Self-reported lifestyle risk factors gathered through survey instruments and interviews, 3) Observed data on all participants’ age, gender, ethnicity, postcode, hip to waist ratio, gathered by trained volunteers. Quantitative analysis of changes in behavioural intention, target behaviours, and measurable CVD risk. The outcome will be assessed at multiple time points after the interventions, once every 3 months, to see whether the behavioural change has been sustained. The per-implementation phase data will provide an insight of the challenges of implementation. Amendment in the design of implementation may tailored accordingly.
(e)Post-intervention qualitative evaluation and feedback

In the post-intervention phase, a qualitative evaluation will be carried out during which the following implementation parameters will be assessed:
The impact on awareness of CVD risks and mitigating measures, amongst disadvantaged populations of a community-based, non-clinical, CVD risk scoring tool and education.The impact of the community based non-clinical CVD risk scoring tool and education on motivational healthy lifestyle among disadvantaged populations.The facilitators and barriers to the adoption of a community-based CVD prevention implementation programme, by target populations.The perspectives of participants regarding their experience and meaning of the intervention.

These will be explored with a subset of intervention participants using focus groups or/and in-depth interview and community mapping. Participants for the qualitative component will include adult volunteers, public health stakeholders and people within the community. The community volunteers will be selected via community organisations and public health stakeholders will be selected from the same area of the research site. Community participants for the qualitative component will be selected via the community volunteers. This post-intervention qualitative study will include purposively selected trial participants.

The number of participants for the qualitative component will be flexible. The number will be determined through the principles of saturation and diversity. However, from each site, we will aim to include at least 12 respondents and a maximum of 30 respondents from different categories [41, 42].

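### At the stated ceiling of 50% attrition, 144 completers need 288 recruits, so the lower part of the 200–300 recruitment range (200–287) falls short

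*Protocol article*

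**What the plan says.** Everything at issue stands in the sample size paragraph of the protocol article, under Eligible population and setting.

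- The calculation is for a stepped wedge design with the InterHEART score as outcome, "90% power for 5% significance", "small effect size (Cohen’s D) = 0.25", "intracluster correlation coefficient of 0.05", "control clusters crossing to intervention in 4 steps", and "participant autocorrelation = 0.7 and cluster autocorrelation = 0.9".
- Its result: "which requires a total of at least 144 persons".
- The inflation for loss: "This needs approximately 200–300 people across the two sites as we expect a high level of attrition (as much as 50"%).
- The screening load: "At least 1500 community members will need to be screened to achieve this recruitment".

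Three other places bear on the point. The item on baseline screening has participants complete the InterHEART score every 3 months. The item on clinical outcome and follow-up defines the primary outcome as the change in risk score among people who complete the assessment and coaching. The Data analysis section plans a cross-classified linear mixed effects model. The number of clusters and the cluster size are not given.

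**The concern.** The requirement, the attrition figure and the recruitment target stand in adjacent sentences, and the third is offered as following from the first two. It follows only for the top of the range. Attrition of 50% is the only loss figure given and the stated reason for inflating, and no lower rate is offered to explain why 200 would do.

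A team that stopped at 200 or 250 would be within the protocol. If the loss then reached the level the protocol itself allows for, fewer people would complete than the calculation calls for. The Discussion section says dropout is likely in this population, so the upper limit is not a remote case. The screening figure is tied to the same range and inherits its looseness.

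**Working it through.** **Step 1: reproduce 144.** Inputs from the sample size paragraph: standardised effect 0.25, intracluster correlation 0.05, cluster autocorrelation 0.9, participant autocorrelation 0.7, 4 steps, 90% power, 5% significance. Assumptions: a two-sided test, a closed cohort, 4 sequences over 5 periods, fixed period effects, total variance 1. With m persons per cluster, the covariance matrix of a cluster's five period means is

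V = 0.05 × (0.9J + 0.1I) + 0.95 × (0.7J + 0.3I)/m,

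where J is the matrix of ones and I the identity. The generalised least squares variance of the treatment effect is the corresponding diagonal element of (Σ X′V⁻¹X)⁻¹, summed over clusters, and power = Φ(0.25/SE − 1.96).

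The number of clusters must be assumed. With 16 clusters of 9 (16 × 9 = 144), SE = 0.0767 and power = Φ(3.26 − 1.96) = 90.3%. Nine is the smallest whole cluster size that reaches 90% with 16 clusters, so the protocol's figure is reproduced. The layout is not unique: 24 clusters of 6 also come to 144, with 91.6%.

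**Step 2: inflate for attrition.** Recruits needed = 144/(1 − 0.50) = 288.

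| Recruits | Left after 50% loss | Largest loss that keeps 144 |
|---|---|---|
| 200 | 100 | 1 − 144/200 = 28% |
| 250 | 125 | 1 − 144/250 = 42.4% |
| 288 | 144 | 50% |
| 300 | 150 | 1 − 144/300 = 52% |

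**Step 3: power if only completers contribute.** With 16 clusters, 100 persons give SE = 0.0900 and power = Φ(2.78 − 1.96), about 79%. With 125 persons power is about 87%, and with 150 about 91%.

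**Step 4: power if partial follow-up is used.** Same model at the individual level: 200 recruits all seen in the first period, dropout rising evenly to 50% by the fifth, missing at random, all observed scores analysed. The timing of dropout is an assumption.

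| Clusters (assumed) | 144 complete persons | 100 complete persons | 200 recruits, even dropout to 50%, partial data used |
|---|---|---|---|
| 4 | 78% | 68% | 77% |
| 8 | 86% | 75% | 86% |
| 12 | 89% | 78% | 89% |
| 16 | 90% | 79% | 90% |
| 24 | 92% | 81% | 91% |

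Under even dropout, 200 recruits carry almost the information of 144 complete persons at every cluster count. If instead the whole 50% leave straight after the first measurement, power with 16 clusters is again about 79%.

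**Step 5: screening.** The article's figures imply a yield between 200/1500 = 13.3% and 300/1500 = 20%. For 288 recruits that means between 288/0.20 = 1440 and 288 × 1500/200 = 2160 people screened.

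**The case against.** The strongest reply has three parts.

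First, the article gives an approximate range and words 50% as an upper limit. Read together, the range could span different levels of loss, with its top matched to the worst case, and 300 × 0.5 = 150 does exceed 144. This stands as far as it goes. A reader might infer that the range fails to cover the requirement at all, and the document does not support that. What remains is that the article attaches no attrition rate to its lower end, so nothing there tells a team that 200 is enough only up to 28% loss.

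Second, a linear mixed model with 3-monthly scores can use what dropouts contributed before leaving, and step 4 shows that this can restore nearly all the power. This is a serious point, and it rules out an unconditional statement that power at 200 recruits is 79%. It does not close the matter. The primary outcome is defined among people who complete, which suggests that leavers do not count, and the sample size paragraph does not rest 200 on partial data.

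Third, a journal article condenses a fuller calculation. That would excuse a missing number of clusters. It does not reconcile three printed figures that disagree over most of the printed range.

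**Conclusion.** The shortfall in completers is certain arithmetic: at 50% loss, any target from 200 to 287 leaves fewer than 144, by 44 at 200 (144 − 100) and 19 at 250 (144 − 125). Only 288–300 meets the plan's own requirement at the one attrition figure it gives.

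The effect on power is conditional. At 200 recruits with the full 50% loss, it is about 79% if only completers contribute and there are 16 clusters (68–81% for 4 to 24). It is about 90% with 16 clusters, 86% with 8 and 77% with 4 if dropout is gradual and all partial data are used. The article fixes neither the cluster count nor the timing of loss, and its outcome definition and its analysis model point in different directions on whether leavers contribute.

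A reader might also infer that 1500 screened is too few. The document does not establish that: the figure is a minimum, and at the 20% yield implied by 300 recruits it covers 288. The inconsistency should be fixed, but it leaves the design and the planned model as they are.

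**What to change.** Replace the approximate range with a target of at least 288 recruits, showing the step 144/0.5, and confirm the screening number for that target together with the yield it assumes. At a 20% yield the need is 1440, so 1500 can stay.

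Alternatively, keep 200 as the minimum and say beside it what supports it: either that the stated 90% power then holds only if attrition is at most 28%, or that the calculation counts the partial follow-up of dropouts. The second route should give the assumed number of clusters and pattern of dropout, and the primary outcome wording should then make clear that non-completers are analysed.

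The change is one sentence. The first option asks for no recruitment beyond the range already stated, and at most 88 people more than its present lower end (288 − 200). The second costs nothing except a more qualified power statement.
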